**Primary objective**

1. To identify the incidence and severity of nasal injury at removal of CPAP in all the three groups (i.e. rotation group, mask continue group, prong continue group) based on the objective scoring and a subjective assessment.

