**MATERIAL & METHODS**

Study site:

NICU, Fernandez Hospital, Hyderabad.

Study design:

A Prospective, Randomized, Comparative study.

Sample size with justification:

Assuming an incidence of nasal injury of 50% among the control group at the removal of CPAP from literature review and previous study from our center^(2-6)^. Assuming three group comparisons with an effect size of 30% with 80% power, alpha error of 5% the sample size calculated is 48 in each group and assuming an attrition rate of 10% we need 55 neonates in each group. Sample size was estimated by using Compare k Proportions: 1- way ANOVA Pairwise test ([www.powerandsamplesize.com](http://www.powerandsamplesize.com)). We will enroll patients till a minimum of 55 infants are enrolled in each group.

Time frame:

From september 2016 to march 2018.

Study population

Neonates admitted in NICU for respiratory distress

Inclusion criteria

- All inborn neonates <=30 weeks of gestation and
- Developed respiratory distress (presence of at least two out of three signs: tachypnea > 60/min, intercostal retractions, and expiratory grunt) within 6 hours of life.

Exclusion criteria

- Patients who have Perinatal depression (5 minute Apgar score of ≤3),
- Patients with Life threatening congenital malformations such as congenital diaphragmatic hernia, and trachea-esophageal fistula, other malformations that would prevent from establishing CPAP due to the anatomical defect such as Pierre-Robinson syndrome and choanal atresia
- Conditions where CPAP would be contraindicated such as neonates with poor spontaneous respiratory efforts or apnea, worsening shock, suspected or proven persistent pulmonary hypertension of newborn, severe metabolic acidosis (pH<7.2 with base deficit > -10), severe respiratory acidosis (pH<7.2 with PaCO2>55mmHg) and massive pulmonary hemorrhage

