**First Randomization**

**Second Randomization**

**Statistical analysis**

Categorical outcome variables will be analysed by Chi square test with continuity correction or Fisher’s exact test. Normal distributed independent variables will be compared by repeated measures ANOVA test whereas a non-parametric test (Mann-Whitney U) will be used for variables with a skewed distribution. An Intention to treat analysis will be done (ITT). All analysis will be done using IBM SPSS version 21 and Microsoft Excel. A P value of less than 0.05 will be considered significant.

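### The sample size of 48 per group assumes 0.0167 per pairwise test, but the analysis section declares significance at a flat 0.05, so the decision rule does not match the sizing.

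*Protocol*

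**What the plan says.** In Material & Methods, the sample size paragraph fixes four inputs.

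- **Control rate:** "Assuming an incidence of nasal injury of 50% among the control group at the removal of CPAP".
- **Effect, power, alpha and result (per arm):** "Assuming three group comparisons with an effect size of 30% with 80% power, alpha error of 5% the sample size calculated is 48".
- **Method:** "Sample size was estimated by using Compare k Proportions: 1- way ANOVA Pairwise test".
- **Enrolment:** "assuming an attrition rate of 10% we need 55 neonates in each group".

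The Statistical analysis section names a continuity-corrected chi-square or Fisher's exact test for categorical outcomes and then gives one threshold: "A P value of less than 0.05 will be considered significant". It mentions no multiplicity adjustment, no overall three-group test for injury incidence and no order of comparisons.

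The Aim asks whether rotation lowers injury against mask or prongs alone, which is two of the three possible pairs. The Outcomes Measured section makes incidence and severity together the primary outcome, and the scoring scheme has four categories (none, mild, moderate, severe).

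**The concern.** A sample size and a decision rule are two halves of one design. If the sizing spends a 5% error over three pairs, each pair must be judged at 0.0167, or some other device must hold the family at 5%. A flat 0.05 does neither.

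A rotation-versus-mask or rotation-versus-prongs P value between 0.0167 and 0.05 would then be positive under the analysis section and negative under the threshold that produced 48. The analyst would have to choose between them, possibly after seeing the data. This is not detail left to a later document: the protocol states a threshold, and its own sample size assumes another.

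**Working it through.** **1. Reproduce the 48.** Inputs from the sample size paragraph: p1 = 0.50, 30-point effect so p2 = 0.20, power 80% (z = 0.8416), alpha 5%. Assumptions: two-sided tests, and an absolute 30 points. A relative 30% (50% against 35%) would need about 223 per group.

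Formula, with alpha shared over τ pairs:

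n = [p1(1−p1) + p2(1−p2)] × [(z(1−0.05/(2τ)) + 0.8416) / 0.30]², where the first bracket is 0.25 + 0.16 = 0.41.

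| τ | Alpha per pair | z | n |
|---|---|---|---|
| 1 | 0.05 | 1.960 | 35.8, so 36 |
| 2 | 0.025 | 2.241 | 43.3, so 44 |
| 3 | 0.0167 | 2.394 | 47.7, so 48 |

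Only τ = 3 gives the protocol's figure. For attrition, 48/0.9 = 53.3, so 54, close to the stated 55.

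**2. Family-wise error of the stated rule: nominal.** Take three equal groups with no true difference, each pair tested at 0.05. For approximately normal estimates, the chance that the range of three exceeds 1.96 × √2 standard errors is 12.2%. For the two rotation contrasts alone it is 9.1%.

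**3. The same, exact.** All binomial outcomes were enumerated at 50% injury in every group. The columns use the two sizes in the protocol and 50, which is about 55 × 0.9 = 49.5, the number expected after attrition.

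| Rule | n = 48 | n = 50 | n = 55 |
|---|---|---|---|
| Three pairs at 0.05, uncorrected chi-square | 12.7% | 13.8% | 11.1% |
| Three pairs at 0.05, continuity-corrected | 8.0% | 8.9% | 7.2% |
| Two rotation pairs at 0.05, continuity-corrected | 5.8% | 6.5% | 5.2% |
| Three pairs at 0.0167, continuity-corrected | 2.8% | 3.2% | 2.6% |
| Overall three-group chi-square at 0.05, then continuity-corrected pairs at 0.05 | 5.4% | 4.8% | 5.3% |

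Fisher's exact test gives the same rates as the corrected chi-square for three pairs at 0.05 with 48 or 55 per group. At 30-40% injury the corrected three-pair rate is 7.4-7.8% for 48 and 55 per group. The flow chart has two rotation boxes. If rotation were twice the size of the others (55/55/110, an assumption), the three-pair rate is 7.7-8.1% continuity-corrected and 9.4-9.9% with Fisher.

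**4. Power per pair, 50% against 20%, exact, continuity-corrected.**

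| Threshold | n = 48 | n = 55 |
|---|---|---|
| 0.05 | 83% | 89% |
| 0.0167 | 69% | 77% |

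Fisher at 0.0167 gives 71% and 78%. The 80% in the protocol is what its uncorrected normal formula delivers at 0.0167, not what the named tests deliver.

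**The case against.** Several points on the other side have force.

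- **The named tests are conservative.** A reader might infer a false-positive rate above 11%. That holds for uncorrected chi-square tests, which the protocol does not name for incidence. With the tests it does name, the three-pair rate is about 7-9%. This stands and sets the size of the point.
- **The aim covers only two pairs.** On those, the corrected test gives about 5-6.5%, close to nominal. This also stands. However, the sizing itself speaks of three comparisons, so a three-pair family is a fair reading.
- **The protocol never calls its 5% family-wise or trial-wide.** That is correct; it follows from reproducing the 48. A pooled formula with two pairs gives 47, which is close but not the stated figure. Even that would split alpha, and so would still disagree with a flat 0.05.
- **A plan not shown might add an overall test or an adjustment.** It might, and the general threshold does not forbid one. The protocol's two sections would still disagree as written.
- **Power to beat both interfaces.** A reader might infer that power is inadequate because, at 0.0167, the chance that rotation beats both mask and prongs is well under 80%. The protocol sets no such target; its 80% fits a single pair. If success required beating both, each test could run at 0.05 without inflating the error of that claim.

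**Conclusion.** The mismatch is real. The sizing rests on 0.0167 per pair and the analysis on 0.05. For injury incidence over three pairs, with 50% injury and no true difference, the family-wise error is about 12% nominally and about 7-9% with the continuity-corrected test, rather than 5%. For the two rotation contrasts it is about 5-6.5% with that test. These figures assume equal groups, two-sided tests and no overall test first.

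Testing severity as part of the primary outcome at 0.05 would add to the error. The amount depends on the mix of injury grades, which the protocol does not give. A reader might infer a definite trial-wide rate from this, but the document does not support one; only the direction is certain.

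**What to change.** In the Statistical analysis section, choose one rule and write it down.

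1. **Overall test first.** Compare injury incidence across the three groups at 0.05, and test pairs at 0.05 only if that result is significant. With exactly three groups this holds the family-wise error at about 5%.
2. **Split alpha.** State that pairwise tests use 0.0167, as the sample size assumes. The stated 80% must then be restated: with continuity correction it is about 69% per pair at 48 per group and 77% at 55.

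Under either option, name injury incidence as the single primary outcome and severity as the first secondary. Say also in the sample size paragraph that the effect is an absolute 30 points and how alpha was divided.

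The cost is a few sentences and no extra infants. The downside is that some pairwise P values below 0.05 will no longer count, and option 2 also carries the lower power shown above.

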**ANNEXURE - 1 :**

**STUDY PROFORMA**

**Title: Can rotation of nasal interfaces decrease the incidence of nasal injury in neonates on nasal CPAP?: A Randomized control trial**

**Screening Form**

| ***Purpose of the form:***   - *This form is meant for all preterm neonates with respiratory distress.* - *Collect the information from the patient file /attendant* | | | | | | | | | | | | | | | | | | | | | | | | | | | | |
| --- | --- | --- | --- | --- | --- | --- | --- | --- | --- | --- | --- | --- | --- | --- | --- | --- | --- | --- | --- | --- | --- | --- | --- | --- | --- | --- | --- | --- |
| **PART A: DETAILS OF THE INFANT (TO BE COLLECTED AT SCREENING)**   - **Please fill the following choices, unless otherwise specified** | | | | | | | | | | | | | | | | | | | | | | | | | | | | |
| S.No | Items | | Response | | | | | | | | | | | | | | | | | | | | | | | | | |
| 1 | Name of the Baby *(in block letters)* | B/o |  |  | |  | |  | | |  |  |  | |  | |  | |  |  |  | | |  | |  | |  |
| 2 | Mother’ Hospital registration number | |  | |  | | | |  | | |  | |  | | | |  | |  | | |  | | | |  | |
| 3 | Baby’s Hospital registration number | |  | |  | | | |  | | |  | |  | | | |  | |  | | |  | | | |  | |
| 4 | Date of birth ***(dd/mm/yy)*** | |  | | | |  | | | | |  | | | |  | | | |  | | | | |  | | | |
| 5 | Time of birth ***(24 hr format)*** | |  | | | | | | |  | | | | | |  | | | | | |  | | | | | | |
| 6 | Birth weight | |  | | | | | | |  | | | | | |  | | | | | |  | | | | | | |
| 7 | Length | | cm | | | | | | | | | | | | | | | | | | | | | | | | | |
| 8 | Sex | | Male/Female | | | | | | | | | | | | | | | | | | | | | | | | | |
| 9 | Head Circumference | | cm | | | | | | | | | | | | | | | | | | | | | | | | | |
| 10 | Resuscitation at Birth | | Y / N  Apgar (a) 1 min_____(b) 5 min______ | | | | | | | | | | | | | | | | | | | | | | | | | |
| 11 | Multiple births | | Single / Twin / Triplet | | | | | | | | | | | | | | | | | | | | | | | | | |
| **Inclusion Criteria** | | | | | | | | | | | | | | | | | | | | | | | | | | | | |
| S.No | Items | | Response | | | | | | | | | | | | | | | | | | | | | | | | | |
| 1 | Gestational age ≤ 30 weeks | | Y / N | | | | | | | | | | | | | | | | | | | | | | | | | |
| 2 | Respiratory distress within 6 hours of life | | Y / N | | | | | | | | | | | | | | | | | | | | | | | | | |
| 3 | Does the baby have all the inclusion criteria? | | Y / N | | | | | | | | | | | | | | | | | | | | | | | | | |
| **Exclusion Criteria** | | | | | | | | | | | | | | | | | | | | | | | | | | | | |
| S.No | Items | | Response | | | | | | | | | | | | | | | | | | | | | | | | | |
| 1 | Abnormalities of upper and lower airways precluding use of CPAP or HHHFNC (Pierre-Robin, Treacher Collins, Goldenhar, choanal atresia, cleft lip/palate) | | Y / N | | | | | | | | | | | | | | | | | | | | | | | | | |
| 2 | Serious abdominal, cardiac, or respiratory malformations including tracheal esophageal fistula, intestinal atresia, omphalocele, gastrochisis, or diaphragmatic hernia | | Y / N | | | | | | | | | | | | | | | | | | | | | | | | | |
| 3 | Required intubation at birth | | Y/N | | | | | | | | | | | | | | | | | | | | | | | | | |
| 4 | Perinatal depression (5 minute Apgar score of ≤3) | | Y/N | | | | | | | | | | | | | | | | | | | | | | | | | |
| **Consent**  ***(If response to all the exclusion criteria is No, obtain consent from parent/ attendant)*** | | | | | | | | | | | | | | | | | | | | | | | | | | | | |
| S.No | Items | | Response | | | | | | | | | | | | | | | | | | | | | | | | | |
| 1 | Written and verbal consent obtained from parent/ direct care taker of the baby? | | Y / N | | | | | | | | | | | | | | | | | | | | | | | | | |
| 2 | If ‘Y’, have you enrolled the baby? | | Y / N | | | | | | | | | | | | | | | | | | | | | | | | | |

**Enrolment Form**

| **Enrolment Number** |  |  |  |
| --- | --- | --- | --- |
| **Group** | **A or B or C** | | |

Group A -Prongs Group B- Mask Group C: Rotation group

| ***PURPOSE OF THE FORM:***   - *This form is meant to be filled only if patient satisfies all the criteria mentioned in screening form* - *Collect information from the file / patient attendant* | | | | | | | | | | | | | | | | | |
| --- | --- | --- | --- | --- | --- | --- | --- | --- | --- | --- | --- | --- | --- | --- | --- | --- | --- |
| **Part A 1 : Details of Mother** | | | | | | | | | | | | | | | | | |
| S.No | Items | | Response | | | | | | | | | | | | | | |
| 1 | Mother’s age in completed years | | years | | | | | | | | | | | | | | |
| 2 | LMP | |  | | | | | | | | | | | | | | |
| 3 | EDD | |  | | | | | | | | | | | | | | |
| 4 | Delivery Details | Normal Delivery | Spontaneous/Induced | | | | | | | | | | | | | | |
|  |  | Instrumental | Forceps/Vacuum | | | | | | | | | | | | | | |
|  |  | LSCS | Elective/Emergency  Indication____________________ | | | | | | | | | | | | | | |
| 5 | Antenatal Steroids | | Y / N  If Yes complete/Partial/Multiple course | | | | | | | | | | | | | | |
| 6 | APGAR score at 1/5/10 min | | / / | | | | | | | | | | | | | | |
| 7 | Intrauterine growth status | | SGA/AGA/LGA | | | | | | | | | | | | | | |
| 8 | Address | | **House number** | | | | | | | | | | | | | | |
|  |  |  | **Street number/ Street name** | | | | | | | | | | | | | | |
|  |  |  | **Locality / VPO / District** | | | | | | | | | | | | | | |
|  |  |  | **City / State** | | | | | | | | | | | | | | |
|  |  |  | PIN CODE |  | |  | | |  | |  | |  | | |  | |
|  |  |  |  |  |  |  |  |  |  |  |  |  |  |  |  |  |  |
|  |  |  | Mobile 1 |  |  | |  |  | |  |  |  | |  |  | |  |
|  |  |  | Mobile 2 |  |  | |  |  | |  |  |  | |  |  | |  |
| **Part A-2: Nutrition** | | | | | | | | | | | | | | | | | |
| S.No | Items | | Response | | | | | | | | | | | | | | |
| 1 | Feeding | | EBM /Partial Breast Feeding/Formula | | | | | | | | | | | | | | |
| 2 | Day of life at which baby is on full feeds | | _______ days | | | | | | | | | | | | | | |
| 3 | Human Milk Fortifiers used | | Y / N Duration _____days | | | | | | | | | | | | | | |
| 4 | IV Fluids | | Y / N Duration _____days | | | | | | | | | | | | | | |
| 5 | Parenteral Nutrition | | Partial/TPN /Not Given Duration of TPN _____days | | | | | | | | | | | | | | |
|  |  | |  | | | | | | | | | | | | | | |
| **Morbidities** | | | | | | | | | | | | | | | | | |
| S.No | Items | | Response | | | | | | | | | | | | | | |
| 1 | Blood culture proven Sepsis | | Y / N Organism_______________ | | | | | | | | | | | | | | |
| 2 | Duration of Antibiotics | | __________________________days | | | | | | | | | | | | | | |
| 3 | Respiratory distress syndrome | | Y / N | | | | | | | | | | | | | | |
| 4 | Study start age (hours) | |  | | | | | | | | | | | | | | |
| 5 | Surfactant | | Y / N | | | | | | | | | | | | | | |
| 6 | Age of giving surfactant (hours) | |  | | | | | | | | | | | | | | |
| 7 | Second dose of surfactant | | Y / N | | | | | | | | | | | | | | |
| 8 | SAS score at time of randomization | |  | | | | | | | | | | | | | | |
| 9 | FiO2 at start of intervention | |  | | | | | | | | | | | | | | |
| 10 | Maximum FiO2 required | |  | | | | | | | | | | | | | | |
| 11 | Flow at start of study | |  | | | | | | | | | | | | | | |
| 12 | Initial choice of interface | |  | | | | | | | | | | | | | | |
| 13 | Age at change of first choice interface (hours) | |  | | | | | | | | | | | | | | |
| 14 | Duration of CPAP ( hours) | |  | | | | | | | | | | | | | | |
| 15 | Duration of Mask as interface ( hours) | |  | | | | | | | | | | | | | | |
| 16 | Duration of Prongs as interface ( hours) | |  | | | | | | | | | | | | | | |
| 17 | Duration of oxygen all forms ( days) | |  | | | | | | | | | | | | | | |
| 18 | Any adverse event during CPAP | | Y / N | | | | | | | | | | | | | | |
| 19 | Maximum nasal injury score | |  | | | | | | | | | | | | | | |
| 20 | Nasal injury score at discharge | |  | | | | | | | | | | | | | | |
| 21 | Pneumonia | |  | | | | | | | | | | | | | | |
| 22 | NEC | | Y / N Stage: _______ | | | | | | | | | | | | | | |
| 23 | PDA | | Y / N Medical / surgical | | | | | | | | | | | | | | |
| 24 | IVH ( grade 3 or 4) | | Y / N Grading________ | | | | | | | | | | | | | | |
| 25 | Cystic PVL (Grade≥2) | | Y / N Grading________ | | | | | | | | | | | | | | |
| 26 | ROP | | Y / N Grading________ | | | | | | | | | | | | | | |
| 27 | ROP requiring laser | | Y / N | | | | | | | | | | | | | | |
| 28 | Supplemental oxygen at 28 days of life, | | Y / N | | | | | | | | | | | | | | |
| 29 | BPD (use of supplemental oxygen at 36 weeks postmenstrual age) | | Y / N | | | | | | | | | | | | | | |
| 30 | Pulmonary air leaks (pneumothorax, PIE) | | Y / N | | | | | | | | | | | | | | |
| 31 | Neonatal mortality | | Y / N | | | | | | | | | | | | | | |
| 32 | Age at discharge (day of life) | |  | | | | | | | | | | | | | | |
| 33 | Weight at discharge (gram) | |  | | | | | | | | | | | | | | |
| 34 | Length at discharge (cm) | |  | | | | | | | | | | | | | | |
| 35 | OFC at discharge (cm) | |  | | | | | | | | | | | | | | |
| 36 | Nasal injury at discharge  Total score:  Grade of injury | |  | | | | | | | | | | | | | | |

**Monitoring chart for nasal injury**

| **Nasal injury** | **Score** | | | | | | | | | | |
| --- | --- | --- | --- | --- | --- | --- | --- | --- | --- | --- | --- |
|  | **Day 1** | **Day 2** | **Day 3** | **Day 4** | **Day 5** | **Day 6** | **Day 7** | **Day 14** | **Day 21** | **Day 28** | **Discharge** |
| **Tip of Nose** |  |  |  |  |  |  |  |  |  |  |  |
|  |  |  |  |  |  |  |  |  |  |  |  |
| **Nasal Septum** |  |  |  |  |  |  |  |  |  |  |  |
|  |  |  |  |  |  |  |  |  |  |  |  |
| **Nostrils** |  |  |  |  |  |  |  |  |  |  |  |
|  |  |  |  |  |  |  |  |  |  |  |  |
| **Nose Shape** |  |  |  |  |  |  |  |  |  |  |  |
|  |  |  |  |  |  |  |  |  |  |  |  |
| **Bridge of the nose** |  |  |  |  |  |  |  |  |  |  |  |
| **Upper lip** |  |  |  |  |  |  |  |  |  |  |  |
| **Total score** |  |  |  |  |  |  |  |  |  |  |  |

| PATIENT END | | | | | MACHINE END | | | | | Interface and settings | | |
| --- | --- | --- | --- | --- | --- | --- | --- | --- | --- | --- | --- | --- |
|  | Distance between cannula& interface-2mm | Nasal skin blanched | Columella/ septal excoriation | Oral/nasal suction done | Bubble present | Temperature normal | Tubings below patient level | Flow rate  5-8 L/min | Water level (Humidifier& Container) | Mask or prong | FiO2 | PEEP |
| 0800 |  |  |  |  |  |  |  |  |  |  |  |  |
| 1200 |  |  |  |  |  |  |  |  |  |  |  |  |
| 1600 |  |  |  |  |  |  |  |  |  |  |  |  |
| 2000 |  |  |  |  |  |  |  |  |  |  |  |  |
| 0000 |  |  |  |  |  |  |  |  |  |  |  |  |
| 0400 |  |  |  |  |  |  |  |  |  |  |  |  |
| Signature |  |  |  |  |  |  |  |  |  |  |  |  |

CPAP Monitoring chart

Name of the baby: MR No: Enrolment No: Group allocated:
